## 4.2 SECONDARY OUTCOMES – ALL PATIENTS

Table 4 shows an example of how the secondary outcomes should be presented and table 5 shows an example of the reporting of the results of the secondary analysis models. Models for the secondary analysis are described in more detail in the relevant subsections. For all models the main visits for comparison will be defined in section 2.2.2, see appendix III for the schedule of assessments.

TABLE 2 DUMMY TABLE FOR THE SECONDARY OUTCOMES

|          | TREATMENT   |           | CONTROL     |           | OVERALL   | MODEL ESTIMATES              |          |       |                |         |
|----------|-------------|-----------|-------------|-----------|-----------|------------------------------|----------|-------|----------------|---------|
|          | (N=)        |           | (N=)        |           |           |                              |          |       |                |         |
|          | AVAILABLE N | SUMMARY   | AVAILABLE N | SUMMARY   | SUMMARY   | EFFECT ESTIMATE  | 95% C.I. | LOWER | 95% UPPER C.I. | P-VALUE |
| Outcome: |             | Mean (SD) |             | Mean (SD) | Mean (SD) |                              |          |       |                |         |
| Baseline |             |           |             |           |           |                              |          |       |                |         |
| 6 months |             |           |             |           |           |                              |          |       |                |         |
| 1 year   |             |           |             |           |           |                              |          |       |                |         |
| 2 year   |             |           |             |           |           |                              |          |       |                |         |
| 3 year   |             |           |             |           |           |                              |          |       |                |         |

1. Relative risk for binary outcomes and adjusted mean difference for continuous outcomes.

For continuous variables this is estimated from the linear mixed effects model, adjusted for baseline measures of the outcome and with random effects for participant and GP practice, and for binary variables this is estimated from a log-binomial regression model, adjusted for GP practice.

#### 4.2.1 POPULATION FOR ANALYSIS

Secondary analysis will also address the secondary endpoints in the ITT population as stated in the protocol. Although the main time points for comparisons are as specified for each outcome, all time points at which an outcome is measured will be incorporated in the model as this will aid with the estimation of treatment effects in the presence of missing data.

#### 4.2.2 THE EFFECT OF ARA IN PATIENTS ON MEASURES OF CARDIOVASCULAR HAEMODYNAMICS

Office measurements of systolic blood pressure (SYSBPR) at baseline, 6 months, 1 year, 2 years and 3 years will be summarised across treatment groups using means and standard deviations. Rates of hypotension (defined in section 2.2.2.1) across the whole study period will be summarised across treatment groups using numbers and proportions of those randomised to each arm. The rates of hypotension across the study period will be analysed by log-binomial regression models and predictors will be treatment allocation and GP practice. The treatment effect will be represented as a relative risk with 95% confidence interval and associated P-value.

The mean change in systolic blood pressure each year from baseline will be analysed with a linear mixed effects model. The model will include systolic blood pressure measurement at each time point and will adjust for baseline measurement and clustering within GP practice will be accounted for as a random effect within the model. An interaction between time and randomised group will be fitted to allow estimation of treatment effect at 6 months and 1, 2 and 3 years. Although 6 months and 1, 2 and 3 years are the main time points of interest, all visits at which BP is recorded will be included in the model to aid estimation of treatment effects in the presence of missing data. The model will also include a patient specific random intercept nested within a practice specific random intercept. Results will be presented as mean difference in change from baseline in systolic blood pressure between the randomised groups at 6 months and 1, 2 and 3 years, with 95% confidence interval and associated 2-sided p value.

The model will include the following fixed effects:

- Time
- Treatment allocation
- Time×treatment allocation
- Baseline systolic blood pressure

The model will include the following random effects:

- GP practice
- Participant ID

The distribution of the change from baseline will be formally assessed for evidence of departure from normality. If necessary, data will either be transformed or analysed using a non-parametric equivalent.

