Appendix II displays the time schedule of trial procedures.

### 2.1 VISIT STRUCTURE

Potentially eligible patients will be invited by their practice to attend a baseline assessment and eligibility visit where the trial will be explained. Informed consent will be obtained and baseline assessments performed. Subsequent assessment will continue for both treatment arms for a further 36 months with follow up visits at weeks 1, 2, 4, 12, 26, and then every 13 weeks to 156 weeks. Windows either side of the visits will be two days for V1 and V2, 4 days at V3 and V4, 7 days for V5 and two weeks thereafter (all calculated from date of randomisation).

Patients will also be supplied with a validated home blood pressure monitoring machine along with an additional diary card, to record their self-assessed blood pressure for one week every 6 months. They will take two readings twice daily (e.g. 2 each morning and 2 each evening) over the week.

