#### 4.2.3 THE EFFECT OF ARA IN PATIENTS ON DECLINE IN RENAL FUNCTION

The decline in renal function will be measured by eGFR and ACR.

eGFR (GFR) at baseline, 6 months and annually will be summarised across treatment arms using means and standard deviations. Mean change in eGFR from baseline to each visit will be assessed using linear mixed models in the same way as for blood pressure.

The model will include the following fixed effects:

- Time
- Treatment allocation
- Time×treatment allocation
- Baseline eGFR

The model will include the following random effects:

- GP practice
- Participant ID

Results will be presented as mean difference in change from baseline in eGFR between the randomised groups at each visit, with 95% confidence interval and associated 2-sided p value.

ACR (ALBCREAT) at baseline and the final visit will be summarised across treatment arm using means and standard deviations. The change in ACR from randomisation to the final visit (visit 15, 3 years) will be assessed using a linear mixed effects model. The model will include baseline ACR and treatment allocation as fixed predictors. Random effects will be participants nested within GP practices. Results will be presented as the difference in mean change in ACR, with a 95% confidence interval and corresponding P-value.

The distribution of the change from baseline will be formally assessed for evidence of departure from normality. If necessary, data will either be transformed or analysed using a non-parametric equivalent.

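### With random intercepts only across up to 15 visits, the 3-year eGFR interval will be too narrow if participants decline at different rates; specify a richer within-participant covariance

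*Combined protocol and SAP*

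**What the plan says.** SAP 4.2.2 sets out the model for systolic blood pressure. The fixed effects are time, treatment, their interaction and the baseline value. On the within-participant structure it says "The model will also include a patient specific random intercept nested within a practice specific random intercept". On the interaction it says "An interaction between time and randomised group will be fitted to allow estimation of treatment effect", without stating whether time is categorical or linear.

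SAP 4.2.3 carries this over to eGFR: "Mean change in eGFR from baseline to each visit will be assessed using linear mixed models in the same way as for blood pressure". The only random effects listed there are GP practice and participant. A confidence interval and P-value are promised at each visit.

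SAP 4.2.1 adds that "all time points at which an outcome is measured will be incorporated in the model". SAP 2.1 gives "follow up visits at weeks 1, 2, 4, 12, 26, and then every 13 weeks to 156 weeks", which makes 15 follow-up visits, and SAP Appendix II schedules a renal profile at each. Neither document mentions a random slope, a residual covariance structure or robust standard errors.

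For ACR, SAP 4.2.3 says: "The change in ACR from randomisation to the final visit (visit 15, 3 years) will be assessed using a linear mixed effects model". Baseline ACR and treatment are the fixed terms, and "Random effects will be participants nested within GP practices".

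**The concern.** A random intercept for participant, with independent residuals of constant variance, implies compound symmetry: one variance for every visit and one correlation for every pair of visits. That is a strong assumption for a measure followed for three years under the heading of decline. If some participants lose eGFR quickly and others slowly, the spread widens with time. The model pools the variance over all visits, five of which fall in the first six months, and applies the pooled value to the 3-year contrast.

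The 3-year difference in eGFR is one of the contrasts the trial will report. If its standard error is too small, its interval is too narrow and its P-value too low. The reverse holds at 6 months. The argument is made for eGFR; no figures are offered for blood pressure, although the wording comes from that model.

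The ACR model has a smaller flaw. With one follow-up value per participant, a participant random effect duplicates the residual.

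**Working it through.** The documents give no SD, slope SD or precision for eGFR, so there is no planned figure to reproduce. What follows is a sensitivity range.

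**Inputs from the documents.** The visit weeks are 1, 2, 4, 12, 26, 39, 52, 65, 78, 91, 104, 117, 130, 143 and 156 (SAP 2.1, Appendix II). In years (week/52), mean t = 1020/(15 × 52) = 1.308 and mean t² = 109846/(15 × 52²) = 2.708. At 3 years t² = 9; at 6 months t² = 0.25. Alpha is 0.05 two-sided (protocol 12.7). Arm sizes of 677 and 695 (Supplementary Table 2) only scale the standard errors and do not affect the ratios.

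**Assumed inputs.** Between-participant SD σb and residual SD σe of 2/4 or 4/4; slope SD σs of 0, 0.5, 1, 2 or 3 ml/min/1.73m² per year; slope-intercept correlation ρ of 0 or -0.5; categorical time; complete data. Practice is left out because randomisation is balanced within practice.

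**Formulas.**
- True variance at time t: V(t) = σb² + σe² + 2ρσbσs·t + σs²·t².
- With categorical time and complete data, the random-intercept model estimates the difference in visit means and uses the average of V over the 15 visits, V̄, at every visit.
- SE ratio (model/true) = √(V̄/V(t)).
- Type I error = 2Φ(-1.96 × ratio).

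**Worked case (4/4, σs = 2, ρ = 0).** V̄ = 32 + 4 × 2.708 = 42.83 and V(3) = 32 + 36 = 68. The ratio is √(42.83/68) = 0.794, so type I error is 2Φ(-1.556) = 12.0%. At 6 months V = 33, the ratio is 1.139 and type I error is 2.6%.

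**Results, ρ = 0.**

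| Slope SD | 3-year type I, 2/4 | 3-year type I, 4/4 | 6-month type I, 2/4 | 6-month type I, 4/4 | 3-year SE, model vs true (4/4) |
|---|---|---|---|---|---|
| 0 | 5.0% | 5.0% | 5.0% | 5.0% | 0.305 vs 0.305 |
| 0.5 | 5.9% | 5.6% | 4.7% | 4.8% | 0.309 vs 0.316 |
| 1 | 8.3% | 7.1% | 3.8% | 4.2% | 0.318 vs 0.346 |
| 2 | 14.6% | 12.0% | 1.8% | 2.6% | 0.353 vs 0.445 |
| 3 | 19.4% | 16.6% | 0.6% | 1.2% | 0.405 vs 0.574 |

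**Check by simulation.** For 4/4 with 5000 simulated trials per setting (n = 300), 3-year coverage was 94.6%, 92.4%, 87.6% and 83.1% for slope SD 0, 1, 2 and 3. The closed form gives 95.0%, 92.9%, 88.0% and 83.4%.

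**Results, ρ = -0.5.** For slope SD 0.5 and 1, 3-year type I error is 4.9% and 6.7% with 2/4, and 4.3% and 4.8% with 4/4. For slope SD 2 and 3 it is again clearly raised: about 9-13% and 15-19%.

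**If time is linear.** For 4/4 and ρ = 0, 3-year coverage falls to 91.2%, 83.2% and 76.6% for slope SD 1, 2 and 3. The SAP's silence on the time term therefore matters.

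**ACR.** Protocol Appendix B and SAP Appendix II schedule urine ACR at baseline and week 156 only, which leaves one outcome row per participant. On simulated data of that form, giving 0, 25, 50, 75 or 100% of the within-practice variance to the participant term produced the same REML log-likelihood (-1415.125), the same treatment estimate and the same SE (0.06434).

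**The case against.** The strongest reply is that nothing in the documents shows that slopes vary enough to matter. That stands: they give no eGFR variability, the error is nil at slope SD 0 and slight at 0.5, and a negative slope-intercept correlation can cancel or reverse it when slopes vary little. A reader might infer that the 3-year interval is too narrow as a matter of fact. The documents support only the conditional statement.

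A reader might also infer that the ACR model cannot be fitted or that its result is unidentifiable. That does not follow. Only the split between participant and residual variance is undetermined; the treatment contrast and its interval are unchanged. The practical risk is a software warning or an unplanned change of model. Skewness in ACR is already covered, since SAP 4.2.3 and 4.8 allow transformation.

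SAP 4.8 does say that alternatives will be considered if assumptions fail. Its detail for these models concerns normality (transformation or bootstrapping), and it gives no covariance check, trigger or fallback.

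SAP 4.7 treats secondary outcomes as exploratory, which limits the consequences. It explains the absence of multiplicity correction but does not justify a miscalibrated interval. SAP 4.4 also relies on the mixed model for validity under missing at random, and that relies in turn on an adequate covariance once visits are missing.

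**Conclusion.** The point holds in conditional form. Random intercepts alone will understate the 3-year eGFR standard error and overstate the 6-month one if rates of decline differ between participants. On the trial's visit grid, with categorical time, complete data, independent slope and intercept, and SDs of 2/4 to 4/4, 3-year type I error is about 6%, 7-8%, 12-15% and 17-19% for slope SD 0.5, 1, 2 and 3. There is no error at slope SD 0. With correlation -0.5 and slope SD 0.5-1, type I error is about 4-7%. All these SDs are assumptions.

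The change is worth making because it is cheap and affects reported intervals and P-values. The ACR matter is clean-up and would not justify a change by itself. These outcomes are exploratory, and the primary Cox analysis does not depend on any of this.

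**What to change.** In SAP 4.2.2 and 4.2.3:

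- State that time is categorical (visit as a factor).
- Keep the fixed effects and the practice random intercept, and replace the participant random intercept with an unstructured within-participant covariance. With 15 visits this has 15 × 16/2 = 120 parameters, so name a fallback order: first a random intercept plus slope for participant, then robust standard errors. Going straight to the random slope would also be acceptable if stated in advance.

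As clean-up for ACR:

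- Drop the participant random effect and keep practice.
- Reconcile the time points. Protocol section 6 and SAP 1.4 list annual ACR change, and SAP Appendix III marks ACR at every visit. Both procedure schedules have baseline and week 156 only, and SAP 2.2.3.2 and 4.2.3 analyse 3 years only.

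The cost is SAP wording, some programming, and 3-year intervals that widen to the extent that slopes vary. With 4/4 and independent slope and intercept, the widening is 0.316/0.309 = 1.02-fold at slope SD 0.5, 0.346/0.318 = 1.09 at 1, 0.445/0.353 = 1.26 at 2 and 0.574/0.405 = 1.42 at 3. The 6-month intervals become narrower in the same settings. The change requires no new data.

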#### 4.2.3 THE EFFECT OF ARA IN PATIENTS ON DECLINE IN RENAL FUNCTION

The decline in renal function will be measured by eGFR and ACR.

eGFR (GFR) at baseline, 6 months and annually will be summarised across treatment arms using means and standard deviations. Mean change in eGFR from baseline to each visit will be assessed using linear mixed models in the same way as for blood pressure.

The model will include the following fixed effects:

- Time
- Treatment allocation
- Time×treatment allocation
- Baseline eGFR

The model will include the following random effects:

- GP practice
- Participant ID

Results will be presented as mean difference in change from baseline in eGFR between the randomised groups at each visit, with 95% confidence interval and associated 2-sided p value.

ACR (ALBCREAT) at baseline and the final visit will be summarised across treatment arm using means and standard deviations. The change in ACR from randomisation to the final visit (visit 15, 3 years) will be assessed using a linear mixed effects model. The model will include baseline ACR and treatment allocation as fixed predictors. Random effects will be participants nested within GP practices. Results will be presented as the difference in mean change in ACR, with a 95% confidence interval and corresponding P-value.

The distribution of the change from baseline will be formally assessed for evidence of departure from normality. If necessary, data will either be transformed or analysed using a non-parametric equivalent.

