## 9.6. Subsequent Visits

Subsequent assessment will continue for both treatment arms for a further 36 months with follow up visits at weeks 1, 2, 4, 12, 26, and then every 13 weeks to 156 weeks. Windows either side of the visits will be two days for V1 and V2, 4 days at V3 and V4, 7 days for V5 and two weeks thereafter (all calculated from date of randomisation). Measurements at each follow-up visit will vary according to the schedule in Appendix B but will consist of a combination of:

- Office BP measurement, using a validated automated device;
- Venepuncture for creatinine & electrolyte levels;
- eGFR (MDRD and CKD-EPI estimations);
- Monitoring for side effects.
- Additional bloods for fasting blood sugar and HbA1c, BNP (where local labs allow), lipids, full blood count and samples for future analysis;
- QoL questionnaires;
- Issue of drug monitoring diary card.
- Urinalysis using albumin: creatinine ratio.
- Home blood pressure measurement recorded on diary card.

Patients will also be supplied with a validated home blood pressure monitoring machine, along with an additional diary card and an instruction sheet, for 1 week every 6 months to document their self-assessed blood pressures. They will take 2 readings twice daily, i.e. 2 each morning and 2 each evening over the

week. The readings for the first two days will be discarded and the mean of the remaining readings taken as the home blood pressure level.

Physicians will be strongly encouraged to manage blood pressure according to NICE CKD guidelines (2008): Blood Pressure Targets: CKD and ACR <70 mg/mmol: systolic blood pressure target of <140 mmHg (target range 120–139 mmHg) and diastolic blood pressure target <90 mmHg. Choice of antihypertensive agents: ACE inhibitors/ARBs if not already prescribed will be offered to people with hypertension and ACR ≥30 mg/mmol. We estimate that around two thirds of patients in BARACK D will be additionally taking an ACE inhibitor or ARB. The remainder, (people with CKD and hypertension and ACR <30 mg/mmol) will be offered a choice of antihypertensive treatment according to the NICE guidance on hypertension (NICE clinical guideline CG127 or its update) to prevent or ameliorate progression of CKD.

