#### 2.2.3.2 TO DETERMINE THE EFFECT OF ARA IN PATIENTS ON DECLINE IN RENAL FUNCTION

##### Endpoint:

Change in Albumin Creatinine Ratio (ACR) (variable ALBCREAT). The percentage change in albumin creatinine ratio from baseline will be computed at 3 years. An increase in ACR level indicates worsening of renal disease. Numbers and percentages with a ≥30% increase in creatinine will be reported.

Change in Estimated Glomerular Filtration Rate (eGFR) (variable GFR). The percentage change from baseline in eGFR from baseline will be computed at 6 months, 1, 2 and 3 years. A reduction in eGFR indicates worsening of renal disease. Numbers and percentages with a drop of  $\geq 25\%$  in eGFR from baseline and  $\geq 20\%$  drop in eGFR from previously reported will also be presented.

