#### 4.3 COVARIATE ADJUSTMENT AND POPULATION

All secondary analyses will account for GP practice as per the primary outcome. These analyses will be carried out on the ITT population.

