#### 4.4 HANDLING MISSING DATA

Data will be analysed using an intention to treat analysis. All randomised patients will be included in the primary analysis up to the last follow-up or primary outcome event as appropriate, assuming non-informative censoring for those withdrawn from the study and not consenting to continued follow-up or those lost to follow-up.

All baseline covariates are expected to be observed. Baseline values will be summarised for those who did and did not complete follow up measurements, separately for those who withdrew completely from the study or were lost to follow-up and those who were withdrawn from medication but consented to further follow-up, in order to assess which observed characteristics are related to missingness. In the unlikely event that there is missing data at baseline then these will be imputed using a suitable method (for example a simple method such as mean imputation if the proportion of missing data is small, i.e. <10%, or the more sophisticated method of multiple imputation if there are substantial missing data at baseline).

For the secondary outcomes mixed models can account for missing data in the outcome at different time points so long as the outcome is observed at least one time point. Although time points for the main comparisons are as specified, all time points at which an outcome is measured will be included in the analysis model in order to aid with estimation in the presence of missing data. This analysis is valid under the missing at random (MAR) assumption, i.e. that the probability of a value being missing depends only on variables included in the model. The missing at random assumption will be tested for each secondary outcome as far as is possible by analysing each baseline covariate in a logistic regression model to determine which if any are associated with missingness (where the outcome is presence/absence of the outcome at the primary endpoint). Should any baseline clinical or demographic variable be predictive of later dropout this variable will be included as an additional covariate in the analysis, in order to ensure the MAR assumption is valid.

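### ACR has one scheduled post-baseline value, so the SAP's mixed model gives it no protection against missing data and the comparison is an available-case analysis

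*Combined protocol and SAP*

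**What the plan says.** **The ACR outcome.** SAP 2.2.3.2 sets a single time point: "The percentage change in albumin creatinine ratio from baseline will be computed at 3 years". SAP 4.2.3 follows it: "ACR (ALBCREAT) at baseline and the final visit will be summarised across treatment arm using means and standard deviations". The model is then specified: "The change in ACR from randomisation to the final visit (visit 15, 3 years) will be assessed using a linear mixed effects model". For its terms, "The model will include baseline ACR and treatment allocation as fixed predictors" and "Random effects will be participants nested within GP practices". The eGFR and blood pressure models have time and time-by-treatment terms; the ACR model has neither.

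**When ACR is taken.** Protocol Appendix B and SAP Appendix II both mark urine ACR at baseline and week 156 only. Protocol 9.6 makes Appendix B the governing table: "Measurements at each follow-up visit will vary according to the schedule in Appendix B".

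**Missing outcomes.** SAP 4.4 states that "mixed models can account for missing data in the outcome at different time points so long as the outcome is observed at least one" of these, and that every measured time point enters the model. Imputation is foreseen only for missing baseline values. The one further step is to add baseline predictors of dropout as covariates. On the population for secondary analyses, SAP 4.3 says "These analyses will be carried out on the ITT population".

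**Text that disagrees.** The objectives tables (protocol synopsis and section 6, SAP 1.4) list change in ACR annually and to the final visit. SAP Appendix III ticks ACR at every visit.

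**The concern.** The argument in SAP 4.4 works for an outcome measured repeatedly: a participant who misses the last visit still supplies earlier values, and the model uses their correlation with the last one. Under the schedules ACR has no earlier post-baseline value. A participant without a week-156 ACR therefore supplies nothing, although the renal profile and office blood pressure are scheduled at up to 14 interim visits.

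ACR is one of the two measures by which SAP 4.2.3 assesses decline in renal function, and it is to be reported with a confidence interval and P-value. The trial is open label, and only one arm has a trial drug to stop when eGFR falls. If that makes absence at week 156 follow renal course differently in the two arms, participants with an ACR value are no longer comparable between arms. Covariates measured at baseline cannot correct for events after it.

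**Working it through.** The documents give no sample size, SD or precision for ACR, so there is no ACR figure to reproduce.

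**1. Share expected to lack the week-156 value.** Inputs: attrition d of 10% in total (protocol 12.3) or 10% per year (SAP 2.4), and planning mortality of 4.76 per 100 person-years for stage 3b (both sections). Over three years the missing share is 1 − (1 − d) × exp(−3m).

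- Protocol attrition, no deaths: 10%. With deaths: 1 − 0.9 × exp(−0.1428) = 22.0%.
- SAP attrition, no deaths: 1 − 0.9³ = 27.1%. With deaths: 1 − 0.729 × exp(−0.1428) = 36.8%.

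**2. What the model reduces to.** With one row per participant, the covariance of the outcomes is σ²(practice) × ZZ′ + [σ²(participant) + σ²(residual)] × I, where Z assigns participants to practices. Only the sum in brackets appears, so the participant variance cannot be separated from the residual. Numerically, four splits of a total of 0.5 (participant part 0, 0.1, 0.25 and 0.4) all gave a log-likelihood of −68.885.

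In a simulated data set of 1,372 participants with about 22% missing, 1,072 rows were used. The practice random-effect model gave a treatment effect of 0.0243 (SE 0.0443); plain available-case ANCOVA gave 0.0241 (SE 0.0441).

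**3. Bias when there is no true effect.** The set-up was 1,372 participants (677 + 695 in Supplementary Table 2) and 300 replicates per scenario. The SD of log ACR (about 1), the within-person correlation (0.7) and the dropout strengths are assumptions. Slopes are log-odds of loss per unit of log ACR, whose SD is about 1. The Monte Carlo error is 0.002 to 0.003.

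| Loss depends on | Slope, standard care / spironolactone | Missing, standard care / spironolactone | Bias, log ACR | Bias ÷ SE |
|---|---|---|---|---|
| Baseline ACR | 0 / 1 | 27% / 27% | 0.001 | 0.0 |
| Interim ACR | 0.7 / 0.7 | 27% / 27% | 0.001 | 0.0 |
| Interim ACR | 0.7 / 0.7 | 20% / 25% | −0.005 | −0.1 |
| Interim ACR | 0 / 0.7 | 10% / 10% | −0.014 | −0.4 |
| Interim ACR | 0 / 0.7 | 27% / 27% | −0.036 | −0.9 |
| Interim ACR | 0.3 / 1 | 27% / 37% | −0.048 | −1.1 |
| Interim ACR | 0.7 / 0 | 27% / 27% | +0.038 | +0.9 |
| Interim ACR | 1 / 0.3 | 27% / 27% | +0.034 | +0.8 |
| Unseen week-156 ACR | 0 / 0.7 | 27% / 27% | −0.089 | −2.1 |

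Negative values favour spironolactone. As ratios, −0.048 is 0.95 and +0.038 is 1.04.

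**4. What post-baseline data recover.** When assumed ACR values at years 1 and 2 were also used, bias fell to 0.001–0.002 in every row except the last, where −0.069 remained. In a separate simulation loss was driven by interim eGFR (assumed: 1,511 per arm; correlation of ACR change with eGFR change −0.2 to −0.6). Imputing ACR from interim eGFR left 0.001 to 0.003. Imputation from the other renal data therefore helps as far as those data explain the loss, and no further.

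**The case against.** **ACR may exist at other visits.** The objectives tables and SAP Appendix III say so. This stands as an inconsistency that must be settled. It does not rescue the plan as written, because both schedules, SAP 2.2.3.2 and SAP 4.2.3 use the final visit only, and the ACR model has no time term through which interim values could enter.

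**An available-case ANCOVA is a respectable analysis.** It keeps participants in their allocated arms and is unbiased when loss depends only on baseline variables in the model. SAP 4.4 also looks for such predictors. That is correct, as the first row of the table shows. What fails is the statement that the mixed model deals with the missing values.

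**Stopping spironolactone is not loss of ACR data.** A reader might infer that the eGFR stopping rule removes participants from the comparison, and might point to the on-treatment denominators in Supplementary Table 2 (331 of 677 against 576 of 695). The documents do not support that. Those figures describe treatment status. Protocol 9.8 continues follow-up after treatment stops where possible, and anyone who attends week 156 stays in the analysis. Protocol 11.4 and SAP 8.5 also require an end-of-study assessment after withdrawal from treatment for an adverse event; whether it includes ACR, or would count as visit 15, is not said. The times at risk in the same table (primary endpoint without PAD) imply only modestly unequal censoring, about 16% against 12% by three years, assuming constant hazards and a three-year maximum.

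**The outcome is exploratory.** SAP 4.7 says so of all secondary outcomes, and the primary result is unaffected. This limits the weight of the point.

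**Conclusion.** The structural point holds on the schedules and SAP 4.2.3. ACR has one post-baseline value, the model is an available-case ANCOVA with a practice effect, the participant random effect is not identifiable, and the missing-data argument in SAP 4.4 does not apply to this outcome. The expected share missing is 10% to 27% before deaths.

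A reader might go further and conclude that the comparison favours spironolactone. The documents do not fix the direction. The sign follows from which arm is assumed to have the stronger link between renal course and loss, and no passage says that renal decline predicts a missed week-156 visit. Under the stated assumptions the bias runs from about −0.05 to +0.04 log units, up to roughly one standard error, when loss depends on values that could be observed. It is about nil when loss depends only on modelled baseline variables, or follows renal course equally in both arms with equal loss. About two standard errors arises only in the scenario where loss depends on the unseen value itself. A change is worth making for a renal outcome that will be published, but it is not critical to the trial.

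**What to change.** 1. Reconcile the ACR frequency in the objectives tables and SAP Appendix III with the two schedules and SAP 4.2.3. If interim ACR values exist, put them into the model with time and time-by-treatment terms.
2. Otherwise, state in SAP 4.2.3 and 4.4 that the ACR model is available-case, drop the participant random effect, and report the number and reasons for missing week-156 ACR by arm.
3. Make the main ACR analysis a comparison of week-156 ACR, on the log scale if skewed and adjusted for baseline ACR, after multiple imputation by arm. The imputation model should use baseline ACR, interim eGFR, potassium and systolic pressure, and whether treatment was stopped.
4. State how deaths are handled. Restricting to survivors is itself a selection after randomisation and should be declared as such.
5. Report the available-case result and an arm-specific delta-adjusted analysis as sensitivity analyses. The second is needed because imputation from observed data does not remove bias when loss depends on the unseen value.

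The cost is SAP wording and a standard imputation run on data already scheduled for collection. The downside is that the ACR result then rests on a stated imputation model, for an exploratory secondary outcome.
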